### Objective

This paper describes the protocol for a comparative effectiveness study of the Breaking the Cycle (BTC) and Maxxine Wright Community Health Centre (MWCHC) intervention programs offered to substance-involved mothers and their young children (0–6 years). This study will explore the effectiveness of the mother-child focused BTC intervention as compared to the mother-focused program of the MWCHC program. More specifically, the study aims to establish the comparative effectiveness and mechanisms of change of the infant mental health components at BTC, as well as estimate the long-term social return on investment (SROI) of BTC. The key research questions it aims to answer are:1a: Do children at BTC demonstrate enhanced infant mental health compared to children at MWCHC up to 2 years post-intervention?1b: Are decreases in exposure to child ACEs, maternal stress, and mental health symptoms and increases in environment scores, parenting attitudes, and mother-child relationship scores greater among mothers at BTC than at MWCHC between pre-treatment and 24-months after engagement?1c: Are lower exposure to psychosocial risk, lower maternal mental health difficulties, and lower maternal stress at baseline associated with enhanced infant mental health scores over time?2a: Are the associations between treatment dose and infant mental health scores mediated by parenting attitudes and the quality of the mother-child relationship?2b: Does child exposure to psychosocial risk moderate the association between treatment dose and child outcomes?3: What is the estimated long-term SROI of the combined mother-child focus and infant mental health components of the BTC program?

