For research question 3, we will adopt international guidelines for SROI [53]. SROI comprises a structured framework to identify, measure, and value the wider societal impacts of an intervention. [53] To support this work, a four-step approach will be adopted: first, using comparative effectiveness evidence from research question 1, information on key mechanisms of change from research question 2, and in partnership with the study’s Steering Committee, we will develop a theory of change to model BTC program inputs, outputs, outcomes, and potential lifetime health and non-health impacts for children engaged in the intervention. Using Microsoft Excel, we will develop a decision analytic model (e.g., decision tree) to link the program theory of change to an economic framework for analysis. We will then undertake a scoping review of the published and grey literature to identify studies and potential data sources that can be used to estimate the monetary value associated with multi-sector program outcomes and impacts (e.g., reduced adverse health and mental health outcomes, improved academic outcomes, and improved economic productivity). Next, we will estimate the costs of implementation of the BTC program based upon the resources required for implementation, as outlined in our theory of change (inputs). Finally, we will combine the evidence on intervention program outcomes and impacts (benefits) and cost of implementation (costs) to yield a benefit-cost ratio, which will provide an estimate of the broader socio-economic returns to society for every dollar invested in BTC. Where there is uncertainty in estimates (e.g., the monetary value that can be attributed to a specific outcome), we will conduct sensitivity and threshold analyses to determine the impact of varying these estimates over a range of acceptable values on the overall SROI calculation. All costs and benefits that are incurred beyond one year will be discounted at an annual rate of 1.5%, in line with Canadian guidelines [21], to estimate the net present value of the SROI [54].

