## Discussion

This study is the first to examine the effectiveness of infant mental health components of a mother-child relationship-focused intervention program on infant mental health outcomes as compared to a mother-focused program. It aims to establish the comparative effectiveness and mechanisms of change of the infant mental health components of BTC, as well as estimate the long-term SROI of the integrated BTC approach. The involvement of MWCHC participants as a control group is a considerable strength of the study, thus making it possible to attribute changes in infant mental health outcomes to the enhanced BTC intervention. Although non-randomized studies suffer from an inherent selection bias, randomization is not possible due to feasibility and ethical reasons. Analytic approaches will be used to minimize any baseline differences between the BTC and MWCHC groups.

It is important to note that while the MWCHC program does not provide the same level of direct intervention with children as the BTC program, children do receive healthcare and well-baby visits. As well, MWCHC mothers receive basic parenting supports and mental health and addiction services that indirectly benefit their children. Their participation in this study will allow them to receive a summary report after every time point, containing an overview of their results as well as a developmental report for their child that they would not have otherwise received. Among other benefits for MWCHC participants, the implementation of the clinical measures will allow for better screening and referral and will increase evidence-based knowledge provided to clinicians. The introduction and embedment of a CBR will also enhance the capacity for research at each site, thus increasing the quality of regular clinical services being offered.

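### As written, the SROI sets benefits measured against MWCHC over the cost of the BTC programme, so the ratio matches neither the components asked about in question 3 nor BTC as a whole

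*Protocol article*

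**What the plan says.** All references are to the protocol article.

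- **Object of the SROI.** In the Objective section, research question 3 reads "What is the estimated long-term SROI of the combined mother-child focus and infant mental health components of the BTC program". The aims in the same section say "estimate the long-term social return on investment (SROI) of BTC", and the Discussion says "estimate the long-term SROI of the integrated BTC approach".
- **Source of the effect.** Under Statistical analysis, the theory of change is to be built "using comparative effectiveness evidence from research question 1, information on key mechanisms of change from research question 2", together with the Steering Committee. Question 1 compares the slopes of the BTC and MWCHC groups through an interaction term. The Design section says the comparison is meant to establish the effect of the infant mental health component that BTC adds.
- **Costs.** "we will estimate the costs of implementation of the BTC program based upon the resources required for implementation", tied to the inputs in the theory of change.
- **Reading of the result.** The benefit-cost ratio is to express "returns to society for every dollar invested in BTC".
- **Sensitivity analyses.** Uncertain estimates, for example monetary values, are varied over a range of acceptable values. No alternative cost basis is named.

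**The concern.** A benefit-cost ratio has a meaning only if benefits and costs are measured against the same alternative. Here the named effect is BTC against another active programme, which provides addiction, mental health, primary care, prenatal and basic-needs services of its own. The named cost is that of the BTC programme, with no statement that shared services, or what MWCHC spends on them, are taken out.

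The SROI is one of the study's stated aims, and a return per dollar is the figure a funder is most likely to pick up. If it is formed as described, it would understate the return on the infant mental health components. It would also leave out whatever benefit BTC's other services bring. The primary outcome analysis is not affected.

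**Working it through.** The article states no SROI, cost or benefit figure, so there is nothing to reproduce. The check sets the two sides of the ratio next to each other and then works out what follows.

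**Step 1: overlap of the programmes (Table 1).** The table has 32 rows. Eleven are marked as offered at BTC only and 32 - 11 = 21 at both sites. Leaving out the 6 rows on target population and structure gives 26 service rows, of which 9 are BTC-only and 17 are shared. The overlap is therefore substantial, but these are counts of features, not shares of cost.

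**Step 2: numerator and denominator against each possible object.**

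| Object | Benefits needed | Costs needed | What the text names |
|---|---|---|---|
| Infant mental health components (question 3) | BTC against MWCHC | BTC-only components | Benefits fit, costs do not |
| BTC as a whole (aims, Discussion) | BTC against no programme | Whole BTC | Costs fit, benefits do not |

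No other named input supplies an effect of BTC against nothing. Question 2 gives mechanisms within BTC, and the scoping review gives monetary values.

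**Step 3: size for the component object.** Let I be the monetised benefit of BTC over MWCHC, C the cost of BTC, and s the share of C spent on services that MWCHC also provides.

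- Planned ratio = I / C
- Matched component ratio = I / [(1 - s) C]
- Planned / matched = 1 - s

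| Assumed s | Planned / matched | Component ratio when the planned ratio is 1.0 |
|---|---|---|
| 0 | 1.00 | 1.00 |
| 0.25 | 0.75 | 1 / 0.75 = 1.33 |
| 0.50 | 0.50 | 1 / 0.50 = 2.0 |
| 0.75 | 0.25 | 1 / 0.25 = 4.0 |

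The values of s are assumptions chosen to show the range. The two ratios agree only at s = 0, which would require the shared services in Table 1 to cost BTC nothing.

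**Step 4: direction for the whole-BTC object.** Let M be the benefit of MWCHC against no programme. The benefit of BTC against no programme is then I + M, and the matched ratio is (I + M) / C. The planned I / C falls short by M / C, so it is too low if M is positive. The Discussion itself says that the supports MWCHC mothers receive benefit their children indirectly. No size can be given, because the study has no untreated group.

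**The case against.** The strongest reply is that the mismatch is partly inferred. The article never states that benefits equal the BTC-minus-MWCHC difference. The evidence feeds a theory of change that is still to be built, and the question 1 model also yields change within BTC. Nor does the article say that the cost is the full cost: it is tied to inputs in that same model. The aims and the Discussion name BTC as a whole, and the Interventions section says its components work together, so whole-programme cost could be the right denominator. Finally, one paragraph condenses an economic evaluation whose full plan is not shown.

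Much of this stands as a limit on how the point may be put. A reader might infer that the SROI is certain to be wrong by construction. The text does not go that far, because both the incremental numerator and the full cost are readings of it, though strong ones. A reader might also take 9 BTC-only rows out of 26 as a cost share of 0.35 and conclude that the ratio is 2.9 times too low (26 / 9). That does not follow, since a home-visiting service and a cooking group each count as one row and the article gives no costs.

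The reply does not remove the point. The article goes beyond leaving detail out: it names an effect source, a cost object and a label, and these do not fit question 3. If BTC as a whole is the object, the counterfactual for benefits is the part that fails. Change within BTC would not supply it, because change over time is not a contrast with no programme. The named sensitivity analyses vary estimates within a structure and do not change the cost basis.

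**Conclusion.** The concern holds for the plan as written. The effectiveness evidence is comparative, the cost is that of the BTC programme, and the ratio is labelled as the return on BTC, while question 3 asks about components and other sections name the whole programme. The resulting ratio answers neither question.

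For the components it is (1 - s) times the matched ratio, and hence too low whenever the incremental benefit is positive and shared services cost something. The factors 0.75, 0.50 and 0.25 rest on assumed s, and the documents allow no single figure. For BTC as a whole it is too low if the services MWCHC provides have positive benefit.

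A reader might go on to infer that a return above 1 will be reported as below 1. That is possible only if the component ratio lies between 1 and 1 / (1 - s), and nothing in the article shows that it does. If the incremental benefit is zero, both ratios are zero and the cost basis makes no difference.

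**What to change.** 1. Reconcile the Objective, Statistical analysis and Discussion sections on one object for the SROI.
2. For question 3, divide the incremental benefit from question 1 by the incremental cost of the components that Table 1 marks as BTC-only. Label the result as the return per dollar invested in those components, not in BTC.
3. Carry the 95% confidence interval of the question 1 effect into the sensitivity analysis.
4. If a whole-BTC ratio is also wanted, keep whole-programme cost but use benefits against no programme. Report it separately and state that this counterfactual is an assumption, since the study does not observe it.

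Costing the BTC-only components is preferable to subtracting MWCHC cost per family from BTC cost per family. That difference would also carry other contrasts between the sites: different provinces, opioid agonist therapy listed among the primary services at MWCHC, and probation and parole services listed at BTC.

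The cost of the change is some extra work to split BTC costs by component. No new participant data are needed.

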### Sample size and power calculations

The study is powered to detect a between-group effect size of Cohen’s d = 0.70 in the primary outcome (change in ASQ-3 between baseline to 24-month post-engagement) for research question 1a. This estimated effect size is conservative compared to the effect size reported in a similar study [55]. Using G*Power v3.1.9.7 [24], assuming a two-sided two-sample t-test with un-pooled variance, we estimate that *N* = 98 participants will be required (*n* = 49 per group). Assuming ~ 30% participant attrition [25], a sample size of *N* = 68 participants with complete data (*n* = 34 per group) achieves 81.1% power (a = 0.05) to detect between-group differences in the primary outcome. Thus, *n* = 50 per group will be sufficient.

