### Primary outcome measures

Informed by the gold standard for assessing and classifying mental health difficulties in the early years (DC: 0–5 [37]), we will use two domains to assess infant/early childhood mental health: (1) socio-emotional functioning and (2) developmental functioning. Measures that provide a diagnosis of mental and physical health problems are not used in the current study due to the infrequency and reliability of these data.

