#### Child’s socio-emotional functioning

Mothers will complete the Ages & Stages Questionnaire: Social-Emotional, Second Edition (ASQ-SE-2) [38] version for children. The ASQ-SE-2 measures a child’s self-regulation, compliance, social-communication, adaptive functioning, independence, and relationships. The version used for the present study consists of a total of 23 items using a three-point scale that includes the option for mothers to indicate whether they feel the behavior is of concern. The ASQ-SE-2 shows good psychometric properties and is widely used in early intervention and mental health programs [39].

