#### Child’s developmental functioning

Mothers will complete the Ages & Stages Questionnaire, Third Edition (ASQ-3) version [40]. The ASQ-3 assesses a child’s development across five domains: communication, gross motor, fine motor, problem solving, and personal-social skills. The version used for the present study consists of a total of 36 items requiring parents to indicate whether their baby exhibits the behaviour regularly, sometimes, or not yet. The ASQ-3 has strong psychometrics properties and is an internationally used developmental screening measure [41].

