### Statistical analysis

All data analyses will be conducted in SAS and Mplus. For research question 1a, linear mixed models will be used to model the change in each of the primary outcomes from baseline to 24-months post-engagement for the BTC and MWCHC groups, controlling for demographic variables that potentially differ at baseline (e.g., maternal age, socioeconomic status, maternal ACEs). Slopes of the two groups will be compared using an interaction term. Linear mixed models can accommodate participants with missing observations [20]. For research question 1b, we will analyze secondary outcomes with a similar approach. For research question 1c, we will conduct regression analyses to predict which risk and protective factors identified at baseline predict change in the primary outcome for the BTC group.

For research question 2, we will conduct a series of mediation (indirect effects) and moderator analyses (interaction effects) for the BTC group, with time in treatment as the independent variable and infant mental health outcomes at 24 months as the dependent variable. Mediator (i.e., maternal behaviour, parenting attitudes, and maternal stress) and moderator (i.e., psychosocial risk) variables at 12 months will be used in all analyses.

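### The primary outcome is two unranked measures in the outcome and analysis sections but one (change in ASQ-3) in the power section, so the 81.1% power and N = 98 cover only the one-outcome reading

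*Protocol article*

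**What the plan says.** Three parts of the protocol article bear on what the primary outcome is.

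- **Primary outcome measures.** The section opens with "we will use two domains to assess infant/early childhood mental health: (1) socio-emotional functioning and (2) developmental functioning". Its subsections assign ASQ-SE-2 to the first domain and ASQ-3 to the second. Neither is ranked above the other. The ASQ-3 is described as covering "development across five domains: communication, gross motor, fine motor, problem solving, and personal-social skills".
- **Statistical analysis.** For question 1a, "linear mixed models will be used to model the change in each of the primary outcomes from baseline to 24-months post-engagement", with the group slopes compared by an interaction term. The outcomes are plural here. For question 1c the same section refers to the primary outcome in the singular.
- **Sample size and power calculations.** The target difference, a Cohen's d of 0.70, is placed "in the primary outcome (change in ASQ-3 between baseline to 24-month post-engagement) for research question 1a". The calculation uses a two-sided two-sample t-test at alpha 0.05. It gives 81.1% power with 34 completers per group, and 98 recruited after about 30% attrition, rounded up to 50 per group. ASQ-SE-2 is not mentioned.

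**The concern.** The number and identity of the primary outcomes is fixed in this article, and it is fixed in two ways. Either ASQ-3 change is the primary outcome and ASQ-SE-2 is something else, or there are two primary outcomes and the sample size was worked out for one of them.

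Question 1a asks whether children in the Breaking the Cycle program show enhanced infant mental health. Suppose one measure favours that program and the other does not. On the power section's wording, the answer turns on ASQ-3. On the outcome and analysis sections' wording, a positive answer could rest on either measure. If that choice is still open when the results are seen, the error rate attached to question 1a depends on which reading is taken. Question 1 also supplies the effectiveness evidence for the social return on investment model, so the ambiguity carries into the benefit-cost ratio.

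**Working it through.** **Inputs from the article (Sample size and power calculations):** d = 0.70; two-sided alpha 0.05; 34 completers per group; attrition about 30%; stated power 81.1%; stated N = 98.

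**Assumptions, because the article gives no figure:** d = 0.70 for ASQ-SE-2 as well; correlation between the two test statistics from 0 to 0.9. The t-test of the power section stands in for the slope interaction in the mixed model.

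**1. Reproduce the stated figures.**
- Degrees of freedom = 2 × 34 − 2 = 66. Noncentrality = 0.70 × √(34/2) = 2.886. Two-sided critical value = 1.997.
- Noncentral t power = 0.8116, against 81.1% stated.
- Recruitment: 34 / (1 − 0.30) = 48.6, so 49 per group and 98 in total, as stated.

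Both figures are correct for a single ASQ-3 comparison.

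**2. Two tests at 0.05, either one counting as success.** If independent, familywise error = 1 − 0.95² = 0.0975. With correlated tests (bivariate normal):

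| Correlation | 0 | 0.3 | 0.5 | 0.7 | 0.9 |
|---|---|---|---|---|---|
| Familywise error | 9.75% | 9.5% | 9.1% | 8.3% | 7.0% |

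Under this rule the power for ASQ-3 itself stays at 81.1%.

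**3. Both must succeed at 0.05.** If independent, joint power = 0.8116² = 0.659. With correlation:

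| Correlation | 0 | 0.3 | 0.5 | 0.7 | 0.9 |
|---|---|---|---|---|---|
| Joint power | 65.9% | 68.3% | 70.3% | 72.8% | 76.3% |

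Under this rule the error rate is not inflated.

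**4. Alpha shared by a Bonferroni split (0.025 each).** The critical value rises to 2.294, and power per outcome at 34 per group is 0.7223. Reaching 80% takes 41 completers per group. 41 / 0.70 = 58.6, so 59 per group or 118 in total, against 50 per group planned.

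**5. Alpha shared by Holm.** ASQ-3 is rejected if its p is below 0.025, or if the ASQ-SE-2 p is below 0.025 and the ASQ-3 p is below 0.05. If independent: 0.7223 + (0.8116 − 0.7223) × 0.7223 = 0.787. By simulation, power for ASQ-3 is 79%, 78% and 76% at correlation 0, 0.5 and 0.9. The chance that Holm's first step rejects at least one outcome is 92%, 86% and 78% at the same correlations.

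**6. Fixed sequence, ASQ-3 first.** ASQ-3 is tested at the full 0.05, so its power stays at 0.8116. ASQ-SE-2 is declared only if both tests are significant, so its chance of success is the joint power in step 3.

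**The case against.** The strongest reply is that the power section already names the primary outcome, that its figures are right, and that success rules and multiplicity usually sit in a full protocol or analysis plan not shown here. Much of this stands. The lack of a multiplicity rule in an article is not in itself a fault, and the design is a non-randomised comparison of two programs. But an unseen analysis plan cannot make two sections of this article agree on how many primary outcomes there are.

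Three stronger readings are tempting, and the article does not support them.

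- **A reader might infer that each outcome will be tested at 5%, so that the stated error rate is wrong.** Alpha appears once, inside the ASQ-3 power calculation. No section gives a test level for ASQ-SE-2 or any familywise rate, so no stated error rate is contradicted. The 7-10% is conditional on unadjusted testing with either outcome sufficient.
- **A reader might infer that the 81.1% is wrong.** It reproduces. It is insufficient only if alpha is split or both outcomes must succeed. No single rule both inflates the error and lowers the power: steps 2, 3 and 4 each show one harm, not two.
- **A reader might count six tests, taking each ASQ-3 domain separately.** The list of five domains describes the instrument. No section plans tests by domain, and the power section treats ASQ-3 change as one quantity. What remains is narrower: the article does not say which ASQ-3 score carries the d of 0.70.

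**Conclusion.** The contradiction holds. The outcome and analysis sections set two unranked primary outcomes, the power section sets one, and the 81.1% and N = 98 belong to the second reading only. ASQ-SE-2, listed first among the primary measures, has no power statement.

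The size depends on the rule that the authors intend. It is nil if ASQ-3 change is the sole primary outcome. It is a familywise error of about 7-10% if either outcome suffices at an unadjusted 0.05, and joint power of about 66-76% if both must succeed. With alpha shared, power is about 72% per outcome (Bonferroni) or 76-79% for ASQ-3 (Holm). All but the familywise error and the 72% for ASQ-3 rest on d = 0.70 for ASQ-SE-2. All but the Bonferroni figures also rest on the assumed correlation.

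**What to change.** Bring the Primary outcome measures and Statistical analysis sections into line with the power section:

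1. Name one ASQ-3 change score, baseline to 24 months, as the single primary outcome, and say which score it is.
2. Place ASQ-SE-2 next in a fixed sequence, tested at two-sided 0.05 only if the ASQ-3 comparison is significant.
3. Use the singular consistently for questions 1a and 1c.

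The familywise error over the two measures is then held at 5%, and 81.1% and N = 98 stand, provided d = 0.70 applies to the ASQ-3 score chosen. The change is one of wording and should be made before outcome data are examined. Its cost is that a finding on ASQ-SE-2 becomes conditional on ASQ-3: its chance of being declared is about 66-76%, against 81% if tested alone at 0.05 (d = 0.70 assumed).

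If the two outcomes are meant to be co-equal, say whether either or both must succeed, state how alpha is shared, and replace the 81.1% with the matching figure from the working. Under a Bonferroni split, 80% power per outcome would need 59 recruited per group instead of 50.
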